#### In-Clinic Recruitment

Clinic staff will identify eligible individuals who visit the clinics for screenings, treatment, or other purposes and will inform them of the study and invite them to participate. In addition, placing flyers in the clinics and displaying the gumball machines in examination rooms will facilitate conversations about the intervention with potential participants. Those who are interested will be given a handout directing them to the intervention website, where they will be invited to complete an eligibility questionnaire and, if eligible, provide consent to participate in the study. Those with a smartphone will be invited to sign up while still at the clinic. Those who are eligible and provide consent will enter the study.

#### Community-Based Recruitment

We will place flyers in bars, other clinics, on mobile testing vans, and at selected community events. The advertisements and flyers include links to the intervention website, where individuals are invited to take the eligibility questionnaire and provide consent.

#### Online Recruitment

We will post advertisements on social networking platforms such as Facebook, Twitter, Instagram, Craigslist, and Grindr (a geolocation-based social networking app used by YMSM).

### Study Design

Owing to potential spillover effects between the treatment and control groups within local peer groups, we deemed a randomized design to be impracticable. Instead, our study will use a quasi-experimental study design with a historical control group consisting of eligible participants identified within the medical records of the same clinics over the 12 months prior to the intervention phase of the study. We preregistered the study (clinicaltrials.gov NCT02946164). All eligible individuals recruited at the clinics, at community-based events, and online will be assigned to the treatment group. We will recruit a minimum of 60 participants and a maximum of 200 participants into the treatment group and identify an identical number of individuals to serve as a historical control group. To our knowledge, this will be the first intervention using gamification to target YMSM for repeat HIV/STI screening. Accordingly, we chose a large sample size range as the upper bound, as it is not possible for us to predict what the demand will be for such an intervention among the target population.

Given the pilot nature of the study, the proposed analyses will likely be underpowered for formal testing purposes. Nevertheless, if we assume that half of the men in the comparison group will attend 1 or more repeat HIV/STI screening visits over 6 months of follow-up, with 60 men in each group, we will have 80% power to detect a minimum change of at least 27 percentage points (from 50% to 77%), which is comparable to the increase observed in an incentive-based intervention previously implemented by the community-based organization that operates the 2 clinics in our study [39].

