**Methods:**

The study consists of a formative research phase to develop the intervention and an implementation phase where the intervention is piloted in a controlled research setting. In the formative research phase, we use an iterative development process to design the intervention, including gathering information about the feasibility, acceptability, and expected effectiveness of potential game elements (eg, points, leaderboards, rewards). These activities include staff interviews, focus group discussions with members of the target population, and team meetings to strategize and develop the intervention. The final intervention is called Stick To It and consists of 3 components: (1) online enrollment, (2) Web-based activities consisting primarily of quizzes and a countdown “timer” to facilitate screening reminders, and (3) in-person activities that occur at 2 sexual health clinics. Participants earn points through the Web-based activities that are then redeemed for chances to win various prizes during clinic visits. The pilot study is a quasi-experimental study with a minimum of 60 intervention group participants recruited at the clinics, at community-based events, and online. We will compare outcomes in the intervention group with a historical control group consisting of individuals meeting the inclusion criteria who attended study clinics in the 12 months prior to intervention implementation. Eligible participants in the pilot study (1) are 18 to 26 years old, (2) were born or identify as male, 3) report male sexual partners, and 4) have a zip code of residence within defined areas in the vicinity of 1 of the 2 implementation sites. The primary outcome is repeat HIV/STI screening within 6 months.

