### Study Population and Eligibility Criteria

Our study targets individuals who (1) are 18 to 26 years old, (2) were born or identify as male, (3) report male sexual partners at the time of enrollment, and (4) have a zip code of residence within defined areas in the vicinity of 1 of the 2 implementation sites. We selected YMSM aged 18 to 26 years as inclusion criteria for this pilot study given the substantial variations in the intervention design that would be required to include adolescent-aged YMSM. Additionally, a minimum inclusion age of 18 years will ensure that participants can provide independent consent to participate in the intervention.

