### Data Collection

For each participant, we will collect data for a period of 6 months following their entry into the study. The primary outcome is repeat HIV/STI screening, defined as the number of screenings participants receive over the 6-month observation period, an indicator of retention in the program and its effectiveness.

In addition, we will collect qualitative information about the experiences of participants and clinic staff, described below. We will use the following methods to collect our secondary outcomes.

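### Clinic, community and online recruits are pooled and compared with clinic attenders only, so *repeat* screening starts from different points in the two groups

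*Protocol article*

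**What the plan says.** **Intervention group.** Study Design states: "All eligible individuals recruited at the clinics, at community-based events, and online will be assigned to the treatment group". The community channel covers bars, other clinics, testing vans and events; the online channel covers social networking platforms. None of the four eligibility criteria requires a previous visit or screen at a study clinic. The nearest is that a man must "have a zip code of residence within defined areas in the vicinity of 1 of the 2 implementation sites". In-Clinic Recruitment adds: "Clinic staff will identify eligible individuals who visit the clinics for screenings, treatment, or other purposes". So even a clinic recruit need not be there to be screened.

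**Control group.** The Abstract describes a "historical control group consisting of individuals meeting the inclusion criteria who attended study clinics in the 12 months prior to intervention implementation". Study Design describes a "historical control group consisting of eligible participants identified within the medical records of the same clinics over the 12 months prior". Study Design also sets the number of controls equal to the number of participants.

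**Time zero and outcome.** Entry follows the web eligibility questionnaire and consent: "Those who are eligible and provide consent will enter the study". Data Collection then says: "For each participant, we will collect data for a period of 6 months following their entry into the study". The primary outcome, repeat screening, is defined there as "the number of screenings participants receive over the 6-month observation period". Outcomes says it is taken from the clinics' own record system. The power statement uses a binary form: one or more repeat visits in 6 months, 50% in the comparison group.

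**The concern.** The word *repeat* presupposes an earlier screen. Each control has at least shown that he uses a study clinic. An off-clinic recruit may never have been inside one, and two things follow from the definitions as written:

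- If he comes once, that first study-clinic screen makes him a success in the binary form and adds one to the count form. It is uptake of a first screen, not a repeat.
- If he never comes, he scores zero. No control can be a man who never attended.

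The first pushes the intervention rate up and the second pushes it down. The contrast therefore mixes recruitment channel with the effect of the intervention. The pilot's first aim is preliminary effectiveness, and the Discussion says the comparison will inform whether further study is warranted. An artefact of either sign could mislead that decision.

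**Working it through.** **1. The plan's own figure.** Inputs from Study Design: 60 per group, 50% in controls, 80% power. Two-sided alpha of 0.05 is assumed, since none is stated. The detectable difference d = p2 - 0.5 solves

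d = 1.96·√[p̄(1-p̄)(1/n1+1/n2)] + 0.8416·√[0.25/n1 + p2(1-p2)/n2] + c,

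where n1 is the number of controls, n2 the number of intervention men, p̄ the pooled rate, and c = ½(1/n1+1/n2) with continuity correction or 0 without. At 60 v 60 this gives about 24.5 points uncorrected and 26.1 corrected. With the correction, 76% gives 79.7% power and 77% gives 83.2%, so 27 is the smallest whole-point change with at least 80% power. The stated figure reproduces and is not in question.

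**2. Size of the mismatch.** The article gives neither the channel shares nor the screening rates of off-clinic recruits, so these are assumptions. Let f be the share recruited off-clinic and q the proportion of them with at least one study-clinic screen in 6 months. Clinic-type men are at 50% and there is no true effect.

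Intervention rate = (1-f)·0.5 + f·q; bias = f·(q - 0.5).

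| f | q = 20% | q = 80% | Bias (points) |
|---|---|---|---|
| 25% | 42.5% | 57.5% | -7.5 to +7.5 |
| 50% | 35% | 65% | -15 to +15 |
| 75% | 27.5% | 72.5% | -22.5 to +22.5 |

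The bias is zero only when q equals the clinic-type rate. The symmetry comes from choosing q evenly around 50%; it is not evidence that the two directions are equally likely.

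**3. Masking a real effect.** If clinic recruits truly reach 77%, with f = 50% and q = 25%, the group shows 0.5·0.77 + 0.5·0.25 = 51%. That is 1 point above the controls.

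**4. Precision of a like-for-like comparison.** Suppose 40 of 60 intervention men have an index screen. Same formula:

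| Controls v intervention | Uncorrected | Corrected |
|---|---|---|
| 60 v 60 | 24.5 | 26.1 |
| 60 v 40 | 27.3 | 29.2 |
| 40 v 40 | 29.5 | 31.7 |

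Check for 60 v 40, uncorrected: p2 = 0.773 and p̄ = (30 + 30.92)/100 = 0.609. The two roots are 0.0996 and 0.0925, and 1.96·0.0996 + 0.8416·0.0925 = 0.273.

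**The case against.** **The bias is already admitted.** The Discussion names time trends and selection bias, disclaims causal statements and calls the control group a benchmark. Study Design says the analyses are likely underpowered. This stands, and it limits how much rests on the comparison. But the admission is general. It mentions neither recruitment channel nor the unequal starting point, and even a benchmark needs the same counting rule on both sides. Unlike a time trend, this part can largely be removed with records already held.

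**Adjustment will deal with it.** Data Analysis adjusts for baseline characteristics. That cannot turn a first screen into a repeat one, and since no control was recruited off-clinic, there is no overlap on channel to adjust across.

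**The magnitude is assumed.** True. Approaching 27 points needs a large off-clinic share and rates far from 50%. Some community or online recruits may already be clinic clients, since they must live nearby.

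**Off-clinic reach is part of what is being piloted.** Also true, and a reason to keep the comparison of all recruits rather than drop it.

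**A stronger reading.** A reader might infer that a screen on the day of enrolment counts as an outcome, because clinic recruits can sign up by smartphone during a visit. The article does not say so. It collects data after entry, and the power statement speaks of repeat visits during follow-up, which points to later visits. The day-of-entry rule and the controls' start date are details that an article may leave to the full protocol, so nothing here rests on them.

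**Conclusion.** The mismatch lies in what the article states: pooled channels, entry at web consent, controls who are all clinic attenders, and an outcome that counts every study-clinic screening after entry. Together these let a first-ever screen count as *repeat* and admit a kind of failure that controls cannot show.

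Neither size nor direction can be determined from the document. With half recruited off-clinic and 20% to 80% of them screened at a study clinic, the bias is -15 to +15 points against the stated 27. This is an illustration, not an estimate. It would be wrong to conclude that the pilot will overstate its effect, or that the comparison is worthless. In a pilot that disclaims causal inference, this is a worthwhile and inexpensive correction to the primary comparison.

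**What to change.** For the effectiveness comparison:

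- Set time zero in both groups at a study-clinic screening visit, and count only later screens over the next 6 months.
- Compare intervention men who had an index screen at or near enrolment, within a window fixed in advance, with controls who had an index screen.
- Adjust for clinic and for the number of earlier study-clinic screens, which the clinic records can supply for both groups.
- Report recruits without an index screen separately, as uptake of a first screen.
- Keep the comparison of all recruits with controls as a secondary analysis, labelled as mixing channels.

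The work is a change of analysis wording and a filter on existing records. The cost is precision. If 40 of 60 intervention men qualify, the detectable difference against 60 controls is about 27 points (29 with continuity correction). If controls are also cut to 40, it is about 29.5 (32). At 60 per group it is 24.5 (26). The stated 27 points should therefore be restated for this comparison, or more controls drawn from the same records, which means relaxing the rule of equal numbers.

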### Outcomes

For the primary outcome of repeat HIV/STI screening, we will use routinely collected client data from the clinics’ electronic patient tracking and medical record system. A set of quantitative and qualitative secondary outcomes will be used to determine the acceptability and feasibility of Stick To It, and whether the intervention is suitable for a future effectiveness study on a larger scale. These implementation outcomes are as follows. First is the ability to recruit the study population: the percentage of eligible men approached who are willing to enroll and whether we can fully enroll the cohort within 6 weeks of study initiation. Second is participant engagement with the intervention: among Stick To It participants, we will determine (1) the proportion who successfully invited 1 or more other eligible individuals to the intervention, (2) the number of completed quizzes, and (3) the average number of quizzes participants completed. Third is cost: we will track the incremental cost of the program, relative to standard of care, which we will identify using the ingredients approach, in accordance with guidance from the World Health Organization [40]. Fourth is the potential for adverse events; that is, whether any adverse events occurred and the potential for adverse events in a larger effectiveness study. Fifth is the cultural competence of staff who implemented Stick To It services and activities and the cultural relevance of the intervention for members of the target population.

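### The historical control group is capped at the number of participants although controls and outcomes come from existing records; if more eligible men are on file, the cap loses precision and forces a selection

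*Protocol article*

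**What the plan says.** Study Design draws the control group from "eligible participants identified within the medical records of the same clinics over the 12 months prior to the intervention phase of the study". On size it states "We will recruit a minimum of 60 participants and a maximum of 200 participants into the treatment group", and for the controls that the team will "identify an identical number of individuals to serve as a historical control group". The wide range for participants is explained by unpredictable demand for a new intervention. No reason is given for tying the number of controls to it.

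The power statement, also in Study Design, assumes that "half of the men in the comparison group will attend 1 or more repeat HIV/STI screening visits over 6 months of follow-up" and continues "with 60 men in each group, we will have 80% power to detect" a change of 27 points, from 50% to 77%. The same paragraph warns that the analyses will probably be underpowered.

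Outcomes says that for repeat screening "we will use routinely collected client data" from the clinics' record system. The abstract describes a "historical control group consisting of individuals meeting the inclusion criteria who attended study clinics in the 12 months prior to intervention implementation" and gives no number. Nothing in the article says how many eligible men the records contain.

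**The concern.** A 1:1 ratio is natural when each control must be recruited and followed. Here a control is a row in a record system, and an additional one needs no contact, visit or incentive. In a pilot that expects low power and looks for a preliminary signal, limiting the cheaper group gives away precision.

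The cap has a second effect. The number of controls equals final enrolment, which can fall anywhere from 60 to 200 and is known only when recruitment closes. The control set therefore cannot be completed before then. If there are more eligible men than participants, some must be left out, and by that time many of their outcomes are already recorded in the system from which they are chosen. A group defined as everyone eligible needs no such choice.

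**Working it through.** **Inputs from the article.** Control rate p1 = 0.50; participants nt = 60 (minimum) or 200 (maximum); controls nc = nt under the cap; power 80%; stated detectable rate p2 = 0.77 (all Study Design).

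**Assumptions.** Two-sided alpha of 5%, not stated for the power figure but in line with the 95% intervals planned in Data Analysis. Control numbers above 1:1 are an illustrative range, because the number of eligible records is not given.

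**Formula.** With d = p2 − p1 and p̄ = (nc·p1 + nt·p2)/(nc + nt):

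- SE0 = √[p̄(1 − p̄)(1/nc + 1/nt)]
- SE1 = √[p1(1 − p1)/nc + p2(1 − p2)/nt]
- Power = Φ[(d − 1.96·SE0)/SE1]
- For continuity correction, d is replaced by d − ½(1/nc + 1/nt).

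**Step 1: the plan's own figure (60 v 60, 50% v 77%).** p̄ = 0.635, SE0 = 0.0879, SE1 = 0.0844.

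- Uncorrected: (0.27 − 0.1723)/0.0844 = 1.158, power 87.7%.
- Continuity-corrected: (0.27 − 0.0167 − 0.1723)/0.0844 = 0.960, power 83.2%.
- Fisher exact: 83.2% at 27 points and 79.7% at 26.

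So 27 is the smallest whole-point difference that reaches 80% by the exact test. The figure reproduces.

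**Step 2: detectable difference with more controls, 60 participants.** The formula is solved for the p2 that gives 80% power. The last column is 1.96·SE1 at 50% v 77%.

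| Controls | Uncorrected | Continuity-corrected | 95% CI half-width |
|---|---|---|---|
| 60 | 24.5 points | 26.1 points | 16.5 points |
| 120 | 21.6 | 22.7 | 13.9 |
| 180 | 20.4 | 21.5 | 12.9 |
| 300 | 19.4 | 20.4 | 12.1 |

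Check of the 120 row: p2 = 0.7156, p̄ = (60 + 42.9)/180 = 0.572, SE0 = 0.0782, SE1 = 0.0740, and (0.2156 − 0.1533)/0.0740 = 0.84, which is 80% power. Power for a 20-point effect (uncorrected) rises from 61% to 73%, 78% and 83% down the rows.

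**Step 3: 200 participants.** The detectable difference (uncorrected) goes from 13.8 points with 200 controls to 12.0 with 400. The gain is smaller but in the same direction.

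**Step 4: the ceiling.** With unlimited controls and 60 participants, SE1 tends to √(0.77 × 0.23/60) = 5.4 points, against 8.4 at 1:1. The participants set the floor, so most of the gain comes from the first few multiples.

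**Step 5: timing.** Phase 2 starts in October 2016, so the control window runs from about October 2015 to September 2016. Six months of follow-up are complete at launch only for index visits up to about March 2016. Follow-up after later index visits runs into the intervention period.

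**The case against.** The strongest reply is that variance is not this study's main problem. The Discussion already rules out causal statements because of time trends and differences between the groups, and it treats the controls as a benchmark. Extra controls narrow the interval around an estimate that may still be biased. That stands, and it limits what the change can achieve.

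It also stands that the gain depends on a number the article does not give. If the records hold no more eligible men than participants, nothing is gained. Extra controls are cheap but not free: male partners and residence area must be established from the records for each man.

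Three stronger readings are tempting, and the article does not support them.

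- **The abstract contradicts Study Design.** The abstract gives no number and does not claim to take everyone eligible. A shorter description is compatible with a subset.
- **Controls will be picked with knowledge of their outcomes.** The article does not say so. A random, consecutive or matched draw would fit its wording, and the selection rule may sit in the full protocol or analysis plan, which are not shown. Nor are all control outcomes complete at launch (step 5). What stands is that the cap creates the need for a selection.
- **The 27 points is wrong.** It reproduces (step 1). The uncorrected 24.5 is a less conservative calculation and does not show an error.

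**Conclusion.** The point holds as a design choice worth changing: Study Design fixes a 1:1 cap without a reason, in a setting where more controls need no patient contact and the plan expects low power. At 60 participants, moving to between 2 and 5 controls each would lower the detectable difference by about 3 to 5 points uncorrected (24.5 − 21.6 = 2.9; 24.5 − 19.4 = 5.1). At 200 participants, moving to 2:1 would lower it by about 2 points (13.8 − 12.0 = 1.8). These sizes rest on a two-sided 5% test, a 50% control rate and, above all, on the records holding that many eligible men. The cap neither makes the comparison invalid nor affects the stated power figure, and removing it would leave the admitted biases in place.

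**What to change.** In Study Design, delete the equal-number clause. Define the control group as every individual in the 12-month window who meets the inclusion criteria, with one index visit each, and make the abstract say the same. Add a pre-specified rule for follow-up that runs past launch. Simply requiring six complete months before launch would roughly halve the window and the pool, so that choice should be made knowingly. Use the adjusted models already planned in Data Analysis.

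If a subset is preferred, fix the ratio in advance, together with a random or matched draw made without sight of the outcomes.

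Keep 27 points as the 60 v 60 worst case, and add the detectable difference for the number of controls actually available once that count is known.

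The cost is a larger record extract, an eligibility check on more records and one added figure. No participant is affected.

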### Outcomes

For the primary outcome of repeat HIV/STI screening, we will use routinely collected client data from the clinics’ electronic patient tracking and medical record system. A set of quantitative and qualitative secondary outcomes will be used to determine the acceptability and feasibility of Stick To It, and whether the intervention is suitable for a future effectiveness study on a larger scale. These implementation outcomes are as follows. First is the ability to recruit the study population: the percentage of eligible men approached who are willing to enroll and whether we can fully enroll the cohort within 6 weeks of study initiation. Second is participant engagement with the intervention: among Stick To It participants, we will determine (1) the proportion who successfully invited 1 or more other eligible individuals to the intervention, (2) the number of completed quizzes, and (3) the average number of quizzes participants completed. Third is cost: we will track the incremental cost of the program, relative to standard of care, which we will identify using the ingredients approach, in accordance with guidance from the World Health Organization [40]. Fourth is the potential for adverse events; that is, whether any adverse events occurred and the potential for adverse events in a larger effectiveness study. Fifth is the cultural competence of staff who implemented Stick To It services and activities and the cultural relevance of the intervention for members of the target population.

